The primary outcome is recurrence-free survival, defined as the time between the randomization date and first occurrence of HCC recurrence, as detected by imaging. Recurrence can be extrahepatic or new intrahepatic. The secondary outcomes of this trial include overall survival, defined as the time between the randomization date and death. If the participant is alive at the end of the study or is lost to follow-up, the last follow-up visit will be used. Other secondary outcomes are virological response, defined as titer of HBV DNA; rate of alanine transaminase normalization; seroreactivity at 24 and 48 weeks after resection, defined as the presence of HBsAg or HBV e antigen; frequency of treatment-related adverse events, as assessed using the Common Terminology Criteria for Adverse Events (version 5.0) [32]; and treatment tolerability, measured in terms of the proportion of patients completing the planned treatment.

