### Sample size

We estimated using PASS 15.0.5 that we would need at least 108 subjects in each group, assuming 3-year rates of recurrence-free survival of 64% among those on entecavir monotherapy [23] and anticipated 79% among those on TDF monotherapy, enrollment lasting two years and follow-up lasting five years. This sample should be able to detect a significant difference between the groups with 90% power and bilateral α = 0.05. We increased the total number from 216 to 240 to compensate for 10% loss to follow-up.

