### Assignment of interventions: allocation

#### Sequence generation

Statisticians will generate randomization cards using stratified randomization according to sex, tumor stage, and preoperative titer of HBV DNA.

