### Statistical methods

#### Statistical methods for primary and secondary outcomes

All statistical analyses will be conducted in a blinded manner. Data will be reported as mean ± SD, and inter-group differences in continuous variables will be assessed for significance using Student's *t* test, while differences in categorical variables will be assessed using the chi-squared test. Survival curves will be calculated using the Kaplan–Meier method and compared using the log-rank test. Cox regression will be applied to identify factors associated with primary and secondary outcomes.

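### Randomisation is stratified by three factors, but the stated primary log-rank comparison does not use them, which costs power if those factors are prognostic

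*Protocol article*

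**What the plan says.** Sequence generation: "Statisticians will generate randomization cards using stratified randomization according to sex, tumor stage, and preoperative titer of HBV DNA".

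Statistical methods for primary and secondary outcomes: Kaplan–Meier curves are to be "compared using the log-rank test". The next sentence gives the Cox model its purpose: "Cox regression will be applied to identify factors associated with primary and secondary outcomes". No stratified or covariate-adjusted comparison of the two drugs is stated, and no effect measure is named as the primary estimate.

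The three factors reappear only under Methods for additional analyses, as subgroups.

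The primary endpoint is time to event (Outcomes): "The primary outcome is recurrence-free survival, defined as the time between the randomization date and first occurrence of HCC recurrence". The Sample size section plans on 64% v 79% free of recurrence at 3 years, 90% power and two-sided 5%.

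**The concern.** Stratified randomisation forces the arms to be alike on the chosen factors. The usual log-rank variance does not know this. It still allows for chance imbalance on those factors, which the design has removed. If the factors predict recurrence, the variance is too large for the design and the test rejects less often than its nominal level. Pooling patients with different underlying hazards also dilutes the contrast between the arms. Both effects reduce power.

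What is at stake is efficiency, in a trial that cannot recover it through enrolment. The Discussion reports that an increase to 638 cases was sought and not approved, so the choice of analysis is one of the few remaining ways to protect the planned 90%.

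**Working it through.** **Reproducing the planned sample size**

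Inputs from Sample size: "assuming 3-year rates of recurrence-free survival of 64% among those on entecavir monotherapy", "anticipated 79% among those on TDF monotherapy", two years of enrolment, five years of follow-up, 90% power, two-sided 0.05.

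- Exponential hazard ratio: ln(0.79)/ln(0.64) = 0.528.
- Schoenfeld events, 1:1 allocation: 4 × (1.960 + 1.282)² / (ln 0.528)² = 103.1, so 104.
- Probability of an event with uniform accrual over 2 years and 5 further years: 0.589 on entecavir, 0.375 on TDF, mean 0.482.
- Patients per arm: 103.1 / 0.482 / 2 = 107.0, against 108 stated. Power at 216 patients is 90.3%.
- Allowance for loss: 216 / 0.9 = 240.

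The stated figure reproduces. Stratifying the test leaves this events-based calculation unchanged.

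**Plain v stratified log-rank**

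The article gives no number of strata, cut-offs, block size or prognostic strengths. The following are therefore assumptions:

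- 240 patients, permuted blocks of 4 within 12 strata: sex 15/85, stage 50/30/20, HBV DNA 50/50.
- Overall 3-year control rate held at 64%; within-stratum hazard ratio 0.528.
- About 10% loss over 5 years; 2 years of accrual, 7 years in total.
- 20,000 runs per cell. The Monte Carlo standard error is about 0.2 to 0.3 points for power, e.g. √(0.9 × 0.1 / 20,000) = 0.2%.

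| Assumed factor hazard ratios (sex; stage, two upper levels; DNA) | Size, plain / stratified | Power, plain / stratified | Effect of ignoring strata |
|---|---|---|---|
| None | 5.0% / 5.0% | 91.5% / 90.4% | +1.1 points |
| Weak (1.2; 1.3 and 1.6; 1.2) | 4.9% / 5.0% | 90.7% / 90.2% | +0.5 |
| Moderate (1.3; 1.7 and 2.5; 1.5) | 3.8% / 4.7% | 88.6% / 89.8% | −1.1 |
| Strong (1.5; 2.5 and 4.5; 2.0) | 2.6% / 4.6% | 82.6% / 88.5% | −5.9 |

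Differences are taken before rounding.

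**Sensitivity to the set-up**

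A second simulation used 216 patients, 8 strata and 3,000 runs per scenario. Power, plain v stratified:

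- stage 2, DNA 1.5, sex 1.2: 87% v 88%
- stage 3, DNA 1.5: 84% v 88%
- stage 3, DNA 2: 82% v 88%

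The size of the plain test was 3.0% to 4.2%. The pattern is the same, and the loss grows with prognostic strength.

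**Sparse strata**

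Under the 12-stratum assumption the mean stratum holds 240/12 = 20 patients. The smallest expected stratum holds 240 × 0.15 × 0.20 × 0.50 = 3.6. This sparsity is why stratifying costs a little when the factors carry no information, and why a pooling rule is needed.

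**The case against.** The best counter-argument is that the article never calls the test unstratified. It condenses a fuller protocol, and an analysis plan that is not shown could stratify the log-rank test, list Cox covariates and set pooling rules. Stratified randomisation followed by a log-rank test is also not a contradiction. This stands in part: the point is not that something is missing. The article does name a primary test and a purpose for the Cox model, though, and neither uses the factors that it chose to balance. A log-rank test with no qualifier is ordinarily read as the plain one.

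The objection on size also stands. The loss depends on prognostic strengths that the article does not give, and in two of the four scenarios the plain test does slightly better. Against that, Background and rationale says preoperative HBV DNA or surface antigen levels are related to recurrence risk, and Methods for additional analyses groups the three factors with others considered prognostic. The balance is uneven: about 1 point at most to lose in the table, about 6 to gain.

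A reader might infer four stronger things that the documents do not support:

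- **That the primary test is invalid.** Its size is at or below 5% throughout the table, so there is no added false-positive risk.
- **That the reported hazard ratio will understate the benefit.** With strong factors, an unadjusted estimate averaged 0.576 against a within-stratum 0.528. But a log-rank test yields no hazard ratio, and the article names no unadjusted one as its estimate. Marginal and within-stratum hazard ratios are in any case different quantities.
- **That the Cox model excludes treatment.** The article neither lists nor excludes it.
- **That the sponsor regards the trial as small.** The Discussion calls the sample large, although it reports the unsuccessful request for 638.

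**Conclusion.** The point holds as an efficiency and specification matter. The stated primary comparison does not use the randomisation strata. The test is valid. If the factors are prognostic it is conservative, with a size of about 3% to 4%, and loses about 1 point of power for moderate effects and about 6 for strong ones. If they are weak or without effect, nothing is lost and stratifying costs about 0.5 to 1 point. The direction follows from the design; the sizes rest on assumed factor strengths, strata and block size. The sample size is not called into question. The change is worth making but is not essential to a valid result.

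**What to change.** In Statistical methods for primary and secondary outcomes:

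- State that the primary log-rank test for recurrence-free survival is stratified by the randomisation factors (sex, tumour stage, preoperative HBV DNA), with the categories used at randomisation. Do the same for overall survival.
- Report the treatment hazard ratio with its 95% CI from a Cox model stratified by, or adjusted for, the same factors. Keep the search for associated factors as a separate analysis.
- Set a rule for pooling sparse strata before the analysts, whom the article describes as blinded, see any outcome data by arm.

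Study site is not a randomisation factor in the article, so this argument does not call for adjusting for it.

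Cost: analysis code and a sentence or two of text. The factors are already needed to randomise. The downside is a small loss of power if they prove not to be prognostic, which the pooling rule limits.

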#### Interim analyses

An interim analysis will be performed after 50% of subjects have completed the 3 months study period. The timing of additional interim analyses will be determined by the Data and Safety Monitoring Board. The committee will not have executive power to stop the trial or modify treatment but can make a recommendation for the former or latter. The Data and Safety Monitoring Board will provide reports of its observations and recommendations to the Trial Management Group and lead Ethics Committee.

#### Methods for additional analyses (e.g., subgroup analyses)

Subgroup analysis will also be conducted according to sex, tumor stage, cirrhosis, preoperative titer of HBV DNA and other factors judged relevant to prognosis.

#### Methods in analysis to handle protocol non-adherence and any statistical methods to handle missing data

Data analysis of this study will according to the intention-to-treat principle. Efforts are made to follow-up participants who dropped out from treatment in order to obtain more evaluation indexes and recorded in the CRFs. The last assessment data will be applied for patients who lost to follow-up.

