#### Criteria for discontinuing or modifying allocated interventions

Titer of HBV DNA in blood will be determined every 12 weeks in all participants. If the titer of HBV DNA has not decreased significantly by 3 months after surgery, which suggests drug resistance, patients who have been receiving 300 mg/day of oral TDF will also be given 0.5 mg/day of oral entecavir, while patients who have been receiving 0.5 mg/day of oral entecavir will switch to only 300 mg/day of oral TDF. Otherwise, patients will continue on the same medication as at enrollment. All participants will receive antiviral therapy until death or the end of the study, given that there are no consensus guidelines on the length of antiviral treatment for patients with HBV-associated HCC. If serum HBV DNA has not decreased after one month of conversion therapy, patients will be switched to tenofovir alafenamide fumarate.

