#### Adverse event reporting and harms

Adverse events will be assessed using the Common Terminology Criteria for Adverse Events (version 5.0) [32]. Adverse events and serious adverse events (SAE) will be recorded including name of adverse event, start time, end time, degree, correlation with study drug, and accompanying treatments. In addition to complying with the requirements of the SAE report of the department, it is also necessary to report to the ethics committee of the principal investigator within 24 h of being informed of the occurrence of SAE. Follow up will carry on until the event is resolved or the condition of the participant return to baseline.

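### A blanket intention-to-treat rule credits adverse events after a protocol-driven drug change to the randomised drug, with no on-treatment safety table beside it

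*Protocol article*

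**What the plan says.** Under the heading on protocol non-adherence and missing data, the protocol article states: "Data analysis of this study will according to the intention-to-treat principle". No outcome is exempted, and no separate safety analysis set is described.

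Under Outcomes, one secondary outcome is "frequency of treatment-related adverse events, as assessed using the Common Terminology Criteria for Adverse Events (version 5.0". No on-treatment window is attached to it.

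Under Criteria for discontinuing or modifying allocated interventions, drug changes are part of the protocol. The trigger is: "If the titer of HBV DNA has not decreased significantly by 3 months after surgery, which suggests drug resistance". The two arms are then handled differently:

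- Entecavir arm (replacement): "patients who have been receiving 0.5 mg/day of oral entecavir will switch to only 300 mg/day of oral TDF".
- TDF arm (addition): "patients who have been receiving 300 mg/day of oral TDF will also be given 0.5 mg/day of oral entecavir".
- Either arm, as a further step: "If serum HBV DNA has not decreased after one month of conversion therapy, patients will be switched to tenofovir alafenamide fumarate".

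Antiviral therapy then continues to death or the end of the study. Under Adverse event reporting and harms, each event is recorded by "name of adverse event, start time, end time, degree, correlation with study drug, and accompanying treatments".

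**The concern.** Analysis as randomised suits recurrence-free survival in a superiority trial and is not questioned here. Harms are different, because this outcome is defined by its relation to treatment. A TDF-related event in a patient switched from entecavir becomes a treatment-related event in the entecavir arm. An event due to added entecavir counts in the TDF arm. An event on tenofovir alafenamide can count in either. Relatedness is recorded to the study drug in the singular, so during combined therapy the record does not show which antiviral was implicated.

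At stake is whether the published safety comparison describes the two drugs or two treatment sequences. The second is a legitimate question, but the article presents the trial as a comparison of two monotherapies.

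**Working it through.** **Inputs from the article.** Conversion is at about 3 months (0.25 year). Follow-up is 5 years (Sample size). 240 patients are randomised 1:1, so 240/2 = 120 per arm. The article gives no adverse event rate and no conversion rate, so there is no figure of its own to reproduce on this point. All rates below are assumptions for illustration.

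**Time off the allocated monotherapy.** A patient who converts at month 3 and is followed for 5 years spends (5 − 0.25)/5 = 4.75/5 = 95% of follow-up on another regimen. This applies to converters only. It also assumes complete observation, whereas Table 1 schedules assessments only until recurrence, metastasis or death.

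**A. A TDF-type event, entecavir-to-TDF switch.** Assume constant hazards and 5-year risks of 3% on entecavir and 10% on TDF.

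- Hazards: −ln(0.97)/5 = 0.00609 per year; −ln(0.90)/5 = 0.02107 per year.
- Risk in a converter: 1 − exp[−(0.25 × 0.00609 + 4.75 × 0.02107)] = 1 − exp(−0.1016) = 9.66%.
- Entecavir-arm risk with share s converting: (1 − s) × 3% + s × 9.66%.

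| s | Entecavir-arm risk | Difference from 10% | Share of the 7-point difference lost | Extra patients with an event among 120 |
|---|---|---|---|---|
| 0% | 3.00% | 7.00 points | – | – |
| 5% | 3.33% | 6.67 points | about 5% | 0.4 |
| 10% | 3.67% | 6.33 points | about 10% | 0.8 |
| 20% | 4.33% | 5.67 points | 19% | 1.6 |

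A second set of assumed hazards (3% per year on TDF, 1% per year on entecavir) gives the same pattern: the difference falls from 9.05 points to 8.62, 8.19 and 7.33, so 95%, 91% and 81% is kept.

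**B. All treatment-related events, both conversion rules.** Assume additive hazards per year: background 1%, TDF +2%, entecavir +1%, with 20% converting in each arm.

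- No conversion: TDF 1 − exp(−0.15) = 13.93%; entecavir 1 − exp(−0.10) = 9.52%; difference 4.41 points.
- Switch only: a converter's risk is 1 − exp[−(0.25 × 0.02 + 4.75 × 0.03)] = 13.71%. The entecavir arm is 0.8 × 9.52 + 0.2 × 13.71 = 10.36%, and the difference is 3.57 points.
- Add-on only: a converter's risk is 1 − exp[−(0.25 × 0.03 + 4.75 × 0.04)] = 17.92%. The TDF arm is 0.8 × 13.93 + 0.2 × 17.92 = 14.73%, and the difference is 5.21 points.
- Both: 14.73 − 10.36 = 4.37 points.

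**C. Equally toxic drugs.** With background 1% and +1.5% for each drug, monotherapy risk is 1 − exp(−0.125) = 11.75%. Risk with add-on from month 3 is 1 − exp[−(0.25 × 0.025 + 4.75 × 0.04)] = 17.82%. If 20% add entecavir, the TDF arm shows a spurious excess of 0.2 × (17.82 − 11.75) = 1.2 points.

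The switch therefore narrows the difference, while the add-on can widen it or create one. Together they can nearly cancel.

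**The case against.** The strongest reply is that nothing in the article says adverse events in particular will be analysed as randomised. That is inferred from one general sentence. Safety populations, and the attribution of events after a treatment change, are commonly left to an analysis plan or full protocol, and neither is shown. This stands as a caveat. It does not remove the point, because the sentence covers the data analysis as a whole: a rule has been stated, and it fits harms badly.

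A reader might go further and infer that the safety comparison is pulled toward no difference, so that a finding of equal safety would be partly produced by the conversion rule. The documents do not support that. TDF patients keep TDF and gain entecavir, so the add-on is not the mirror image of the switch, and calculations B and C show that all-event counts can move either way. Nor does the article state an equal-safety hypothesis.

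The effect may also be small. Only virological non-responders convert, and calculation A amounts to at most 1.6 extra patients per 120 at 20% conversion. That is fair, but the trigger is not quantified in the article, so rarity cannot be presumed.

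Event start and end times and accompanying treatments are collected, so the drug at onset can largely be reconstructed if conversion dates are held. This stands too. What cannot be recovered is relatedness to each of two antivirals taken together.

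Finally, an analysis by drug taken has its own selection bias, since converters are chosen by virological non-response. That is correct, and it is a reason not to replace the as-randomised table.

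**Conclusion.** The point holds in a limited form. Taken literally, the single analysis rule and the built-in drug changes credit treatment-related adverse events after conversion to the randomised drug. Differences in drug-specific events are diluted, and total events in the TDF arm may be inflated by the add-on, so the net direction is not predictable. On assumed 5-year risks of 10% and 3%, about 5% to 19% of a TDF-type difference is lost when 5% to 20% of the entecavir arm converts. The true size is unknown, because the documents give neither a conversion rate nor an event rate.

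The documents do not support the stronger conclusion that the design biases safety toward equality. The priority is minor: this is a secondary outcome, and the primary comparison is unaffected.

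**What to change.** In the section on non-adherence and missing data, state that the as-randomised adverse event table will be accompanied by an on-treatment table. It would give events and exposure time on the allocated monotherapy up to conversion, with events after conversion listed separately by regimen (TDF after entecavir, TDF plus entecavir, tenofovir alafenamide). Neither table need be declared primary.

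In the section on adverse event reporting, add the antiviral(s) being taken at onset and the relatedness to each.

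The cost is one extra table and a small addition to the CRF. The CRF change is best made early: recruitment was under way at protocol version 1.1, and the Data management section says signed forms can no longer be altered. The downside is that the on-treatment table is not fully protected by randomisation, because conversion depends on virological non-response. Showing both tables lets the reader see this. No change to the treatment rules is implied.

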#### Plans to give access to the full protocol, participant-level data, and statistical code

Full protocol, participant data, and statistical code of this study will be accessed for grant public after the full paper of this study is published.

### Oversight and monitoring

#### Composition of the coordinating center and trial steering committee

The trial management will be conducted under the auspices of the Guangxi Medical University Cancer Hospital in accordance with the current standards of GCP in China and the protection of subjects’ rights and interests in accordance with the Declaration of Helsinki.

#### Composition of the data monitoring committee, its role, and reporting structure

The data monitoring committee is composed of the GCP of Guangxi Medical University Cancer Hospital. The office staff of GCP will be in regular contact with the researchers to follow up on the progress of the trial and address any questions they may have. The CRF is reviewed by the staff to check for consistency with the study protocol, data consistency, missing data, and scheduling. If the patient consents, the investigator will need to send a copy of the signed informed consent to the office of GCP for review. When there is a problem with the data, the office of GCP will ask the investigator to provide a data description sheet to supplement or explain the data inconsistency, missing data, etc. Any significant issues identified during monitoring are reported, as appropriate, to the trial management team and the relevant authorities, including serious breaches of the GCP and/or the study protocol. The investigator shall be subject to monitoring, auditing, ethical review and management inspections related to the trial, and shall provide the original data and documentation of the trial.

#### Adverse event reporting and harms

Adverse events will be assessed using the Common Terminology Criteria for Adverse Events (version 5.0) [32]. Adverse events and serious adverse events (SAE) will be recorded including name of adverse event, start time, end time, degree, correlation with study drug, and accompanying treatments. In addition to complying with the requirements of the SAE report of the department, it is also necessary to report to the ethics committee of the principal investigator within 24 h of being informed of the occurrence of SAE. Follow up will carry on until the event is resolved or the condition of the participant return to baseline.

